### Recruitment Procedure

#### Physician Recruitment

The lead physician (or research administration staff) of the recruitment site is first approached by email regarding their interest in the study, and a 20-30 minute presentation is offered as a way to disseminate the study details and gauge interest across the site. If the lead physician is interested in participating, they contact the clinicians within their site, disseminate information regarding the study, and identify the clinicians interested in participating in the study. Upon receiving REB approval, a staff member at the participating site generates a list of eligible participants and has the list vetted by the respective physicians for appropriateness.

#### Patient Recruitment

The participating sites send invitation letters to eligible and appropriate participants, explaning the study goals and protocol. The letter invites participants to contact the study coordinator directly, either by email or phone call, if they are interested in participating in the study. Upon initial contact, the study coordinator describes the study and answers any of the patient’s study-related questions. If the respondent is interested in participating, the coordinator will schedule an appointment with the respective clinic, and email or mail the patient the consent form in advance for review.

### Data Analyses

The principal analysis strategy will be the use of linear mixed models in the Statistical Analysis System (Cary, NC, USA) using the PROC MIXED procedure. This approach provides a simple method to incorporate baseline values and the correlation of each participant over time (using a random effect). This model is more powerful than the repeated measures *analysis of variance*, as it can easily examine differences between the RCT groups at all time points, and can accommodate potential confounders. Furthermore, although the A1c measurements will be made at 3-month intervals, our primary analysis will focus on A1c levels at the conclusion of the 12-month study. A contrast will be constructed to test this primary comparison among all possible pair-wise tests; no adjustments for multiple testing will be required. Subsequent adjustments will be made for potential confounding variables as necessary, such as baseline parameters that may vary between groups (eg, age, sex).

Secondary contrasts will be used to examine differences from baseline for all other time points; however, these will be of exploratory interest only. Moreover, we will use regression analysis to separate the contribution of the different intervention components (activity monitor, weight scale, SMBG, mobile app features), and determine their independent effects on the primary outcome at 12 months. This approach will identify which aspect of the mHealth intervention contributed to the change in A1c.

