### Participants

The inclusion criteria for participants include: definitive diagnosis of T2DM, not treated with insulin, at least 18 years of age, a baseline glycated hemoglobin A1c (A1c) of 7.5% or higher, and ability to speak and read English.

Exclusion criteria include: inability to use a mobile phone (eg, due to vision problems) or to comply with home monitoring (eg, due to suffering from anxiety or depression), and duration of diabetes under one year. Participants who have had diabetes for less than one year are excluded because they typically demonstrate a higher adherence to self-care and have high levels of motivation [12].

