### Outcomes

The primary outcome measure is change in A1c from baseline to 12 months. Each recruitment site is provided with a DCA Vantage Analyzer (Siemens, Munich, Germany) point of care A1c device to reduce the variability in the A1c laboratory assays. As secondary end points, A1c measurements are also collected at 3-month intervals (3, 6, and 9 months). Clinical staff within the patient’s circle of care are conducting the point of care A1c tests.

Secondary outcomes include blood pressure (mmHg), weight (pounds), total cholesterol (mmol/L), Low Density Lipoprotein cholesterol (mmol/L), and weight at baseline, 3, 6, 9, and 12 months. The number of participants who achieve optimal glycemic control (A1c <7%), as well as the type and frequency of medication changes, will also be measured. Furthermore, validated instruments described in Table 1 are being used to collect and measure burden of disease and diabetes-related self-efficacy and self-care, pre-, mid-, and post-study.

**Table 1 table1:** Validated instruments administered pre-, mid-, and post-study.

Measure	Description
Diabetes Distress Scale (DDS)	The DDS is a 17-item instrument that assesses the emotional, physician-related, regimen-related, and interpersonal aspects of diabetes distress, and provides an indication of diabetes-related quality of life [13].
Diabetes Empowerment Scale - Short Form (DES-SF)	The DES-SF is a 28-item instrument used to measure psychosocial self-efficacy of diabetes self-management. This tool focuses on (1) managing diabetes, (2) assessing readiness to change, and (3) willingness to set goals and change behaviors [14,15].
Summary of Diabetes Self-Care Activities (SDSCA) measure	The SDSCA is a 11-item instrument that assesses individual levels of diabetes self-care, focusing on general diet, specific diet, exercise, medication adherence, blood-glucose testing, smoking, and foot care [16].
The Mobile Application Rating Scale (MARS) App - User Version	The MARS is a 26-item instrument used to evaluate the quality, functionality, and overall satisfaction of the mobile app itself [17].

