### Sample Size

The sample size estimation was based on detecting a minimum reduction of 0.5% in A1c values. Given our inclusion criteria of A1c >7.5%, we anticipate that A1c levels will be highly clustered around 8.5% (standard deviation 1.0). A minimum of 63 participants per group is necessary to detect a difference of 0.5% in A1c, at an 80% power with a one-sided 5% significance level in all anticipated cases. With a further 15% adjustment for potential dropouts, a final sample size of 150 subjects will be required for both groups, with 75 participants in each study arm. All calculations were performed using the R software package, *epibasix* [18].

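### If the random effect in the A1c model is a participant intercept alone, the test of 12-month change can exceed its nominal type I error

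*Protocol article*

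**What the plan says.** The Outcomes section states: "The primary outcome measure is change in A1c from baseline to 12 months". It adds that "A1c measurements are also collected at 3-month intervals (3, 6, and 9 months", so there are five A1c visits including baseline. The Data Analyses section names "linear mixed models in the Statistical Analysis System (Cary, NC, USA) using the PROC MIXED procedure" and says the approach can "incorporate baseline values and the correlation of each participant over time (using a random effect". It then says that "our primary analysis will focus on A1c levels at the conclusion of the 12-month study", tested by a contrast.

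The section does not say whether the random effect is an intercept or includes a slope. It neither names nor excludes a residual covariance structure or robust standard errors. It also leaves open whether baseline enters as a covariate or as a fifth response. The Sample Size section gives a single SD of 1.0 and no correlation between visits.

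**The concern.** The article does not leave within-participant correlation open: it names a random effect as the means of carrying it. The simplest reading is a participant random intercept with independent residuals, which is compound symmetry. The covariance between baseline and month 12 is then taken to equal that between months 9 and 12.

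The true variance of a 12-month change depends on the baseline and 12-month measurements alone. The model instead uses averages over all five variances and all ten pairs. If correlation weakens with the gap, the 0-to-12 correlation lies below the average, and the standard error of the primary contrast is understated. The p-value and confidence interval are then too favourable, and a larger sample does not cure this.

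**Working it through.** **Inputs from the article.** Visits at 0, 3, 6, 9 and 12 months (Outcomes); difference 0.5, SD 1.0, 63 per group, 15% dropout, 75 per arm (Sample Size); test level as stated, "at an 80% power with a one-sided 5% significance level in all anticipated cases".

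**Assumed inputs.** All visit correlations and visit-specific SDs. The article gives none, so a range is shown.

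**The plan's own figure.** n per group = 2(z_alpha + z_beta)² SD² / 0.5².
- Two-sided 5%: 8 × (1.960 + 0.842)² = 62.8, so 63.
- One-sided 5%: 8 × (1.645 + 0.842)² = 49.5, so 50.
- Dropout: 63 / 0.85 = 74.1, so 75 per arm.

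The stated 63 is the two-sided figure although the text says one-sided. That is a separate matter, but it is why both versions appear below for the change contrast.

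**Formulas.** Let S be the true 5 × 5 covariance, with complete data and a separate mean for each arm and visit. A random-intercept model estimates one variance (the mean of the diagonal of S) and one covariance (the mean off the diagonal). Let r be the model-based SE divided by the true SE.
- (A) Change from baseline: r² = 2(mean variance − mean covariance) / (S₀₀ + S₁₂,₁₂ − 2S₀,₁₂).
- (B) Unadjusted 12-month level: r² = mean variance / S₁₂,₁₂.
- (C) 12-month level with baseline as covariate, one common slope b: r² = mean residual variance over the four later visits / residual variance at month 12.
- Actual type I error = sides × [1 − Φ(z × r)].

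**One case by hand: AR(1), 3-month correlation 0.8, equal SDs.**
- The ten correlations are 0.8 (four), 0.64 (three), 0.512 (two) and 0.4096 (one). Their mean is 6.5536 / 10 = 0.655.
- (A) True over model variance = (1 − 0.410) / (1 − 0.655) = 0.590 / 0.345 = 1.71. The true SE is 1.31 times the model SE, so r = 0.764. One-sided: 1 − Φ(1.645 × 0.764) = 10.4%. Two-sided: 2[1 − Φ(1.960 × 0.764)] = 13.4%.
- (B) All variances are equal, so r = 1 and the error is 5.0%.
- (C) b = (0.8 + 0.64 + 0.512 + 0.4096) / 4 = 0.590. Residual variances 1 − 2b·c + b² are 0.404, 0.593, 0.744 and 0.865, with mean 0.651. r = √(0.651 / 0.865) = 0.868, which gives 7.7% one-sided.

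**Range of assumptions (type I error in %, nominal 5%).**

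| Assumed truth | r for A | A one-sided | A two-sided | B one-sided | C one-sided |
|---|---|---|---|---|---|
| Constant 0.6, equal SDs | 1.000 | 5.00 | 5.00 | 5.00 | 5.00 |
| Linear fall 0.75 to 0.60, equal SDs | 0.866 | 7.72 | 8.96 | 5.00 | 6.55 |
| Linear fall 0.80 to 0.50, equal SDs | 0.775 | 10.13 | 12.90 | 5.00 | 7.75 |
| AR(1) 0.7, equal SDs | 0.795 | 9.55 | 11.91 | 5.00 | 6.86 |
| AR(1) 0.8, equal SDs | 0.764 | 10.44 | 13.43 | 5.00 | 7.67 |
| AR(1) 0.9, equal SDs | 0.735 | 11.35 | 14.99 | 5.00 | 8.63 |
| Constant 0.6, SD 1.0 falling to 0.8 | 0.985 | 5.26 | 5.36 | 3.17 | 3.59 |
| Constant 0.6, SD 1.0 rising to 1.2 | 0.990 | 5.18 | 5.24 | 6.54 | 6.14 |
| Constant 0.6, baseline SD 0.8, later 1.0 | 1.052 | 4.18 | 3.93 | 5.65 | 5.00 |

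**Simulation check.** REML fits, 75 per arm, 15% random dropout, 1,500 trials per setting (Monte Carlo SE about 0.8 points near 10%, since √(0.1 × 0.9 / 1500) = 0.0077).
- AR(1) 0.8: change contrast 10.1% one-sided and 12.1% two-sided; level contrast 4.8% and 4.7%.
- Constant 0.6: change contrast 4.9% one-sided.
- SD falling to 0.8: level contrast 3.1% one-sided.
- SD rising to 1.2: level contrast 7.1% one-sided.

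Reading C was not part of this check.

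**The case against.** The best defence is that the article says only that a random effect is used, in parentheses. It does not say that this is the sole covariance term, and PROC MIXED allows a residual structure, a random slope or robust standard errors alongside it. Such detail is commonly left to an analysis plan, and none is shown. This stands in part: intercept-only is an inference from the wording. Still, the article names the device that carries the correlation, so the point addresses a stated choice and not a silence.

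The second defence is that the Data Analyses section speaks of A1c levels at 12 months. For an unadjusted level contrast with equal variances the test holds 5% under any correlation pattern. This also stands, but that reading does not match the change outcome in the Outcomes section, and the stated intention to incorporate baseline points away from it.

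A reader might go further and infer that the primary standard error is bound to be too small. The documents do not support that. They give no visit correlations or SDs, and some plausible covariances leave the test exact or conservative. A reader might also argue that the entry criterion, "a baseline glycated hemoglobin A1c (A1c) of 7.5% or higher", compresses baseline spread and so adds to the inflation. The article does not report how spread changes after entry. With a smaller baseline SD and constant correlation, the change contrast is in fact slightly conservative (4.18% one-sided in the table). Finally, the 13% to 15% values are two-sided, whereas the stated test is one-sided.

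**Conclusion.** The point holds as a conditional one. It needs three conditions: a random intercept as the only source of correlation, a contrast that uses baseline (as change or as covariate), and correlation that falls over the year. With equal variances and the decay patterns tried, a nominal one-sided 5% test then runs at about 8% to 11% for change and about 7% to 9% with baseline as covariate. Under AR(1) 0.8 the two-sided figure for change is about 12% to 13%.

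Nothing in the article justifies relying on constant correlation across 12 months, so the validity of the primary test should not depend on it. Whether the finished analysis would be affected cannot be determined from this document.

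**What to change.** In place of a lone random intercept, specify visit as a categorical factor with arm-by-visit means and an unstructured within-participant covariance: `REPEATED visit / SUBJECT=participant TYPE=UN`, with `DDFM=KR`. Test the arm contrast at month 12, and say whether baseline is a response (contrast of change) or a covariate, so that the contrast matches the primary outcome. With complete data and baseline as a response, this reduces to comparing mean change between arms using the observed variance of change, so no assumption about the other visit pairs enters.

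Name a fallback for non-convergence in advance: `TYPE=TOEPH`, or a random intercept with empirical (robust) standard errors. The second repairs the standard error, but with missing visits it still weights earlier data by the compound-symmetry structure.

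The cost is 15 covariance parameters for five visits (5 × 6 / 2) instead of two, which about 150 participants easily support, and possibly a slightly wider confidence interval. No change to data collection is needed.

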## Methods

### Trial Design

The *bant2* study is a 12-month, prospective, multicenter, unblinded, parallel RCT in which 150 participants are randomly assigned to one of two groups: the control group receives current standard of care, and the intervention group receives the mobile phone app system in addition to standard of care. During the study period, all participants (intervention and control) attend quarterly clinic visits (standard care) and receive usual care.

The primary recruitment strategy for this study is through self-referral at primary care and community practices throughout the Greater Toronto Area. This area includes sites that are situated in urban and suburban settings. The University Health Network Research Ethics Board (REB) approved the study (14-7978-AE). Local institutional REB approvals were also obtained from the following participating sites: St. Joseph’s Health Care Centre (#2015-010), Trillium Health Partners (#698), and North York General (#15-0038). For sites without an institutational REB, namely the Taddle Creek Diabetes Education Program and LMC Diabetes and Endocrinology, approval was obtained from an Institutional Review Board (Pro00016415).

Randomization is being conducted at the patient level, using random block sizes of four and six to reduce the variance across the entire sample, with a 1:1 allocation ratio. Stratificaiton is also conducted by recruitment site. The allocation envelopes contain a piece of paper with either *control* or *intervention* written upon it, as well as a random patient identifier. The study coordinator allocates each participant by taking the envelope on the top of the stack, and enrolls the participant into the appropriate study arm, as indicated.

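### Further covariate adjustment is triggered by observed baseline differences between arms, and the plan does not say whether the initial or the adjusted 12-month estimate decides

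*Protocol article*

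**What the plan says.** The principal analysis is a linear mixed model. The Data Analyses section says of it: "This approach provides a simple method to incorporate baseline values and the correlation of each participant over time (using a random effect"). Part of its justification is that it "can accommodate potential confounders". The section then fixes the target: "our primary analysis will focus on A1c levels at the conclusion of the 12-month study". One contrast tests that comparison, without multiplicity adjustment.

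The next sentence is the one at issue: "Subsequent adjustments will be made for potential confounding variables as necessary, such as baseline parameters that may vary between groups (eg, age, sex"). Age and sex are examples, not a closed list. The article gives no threshold for a difference and no time at which the choice is made. It does not say whether the contrast before or after these adjustments is the trial's answer.

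Under Trial Design, allocation is randomized "with a 1:1 allocation ratio" and "Stratificaiton is also conducted by recruitment site". Site is not named as a model term.

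**The concern.** Under sound randomization a baseline difference between arms is a chance event, not confounding that needs removal. Covariates are worth including because they predict the outcome, and that can be judged before any data are seen. A rule keyed to observed differences selects on the wrong property and makes the adjusted model vary from one realization of the trial to the next.

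Two things are at stake. Followed strictly, the rule leaves out useful covariates whenever they happen to be balanced, and so loses precision. Followed loosely, it permits a choice among several adjusted results, with no rule for which counts if they disagree. The plan forgoes multiplicity adjustment because it expects a single primary comparison. That expectation needs one identified estimate.

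**Working it through.** **The plan's own figures.** The article gives no number for the covariate rule. The arm size used below comes from Sample Size: "A minimum of 63 participants per group is necessary to detect a difference of 0.5% in A1c", with SD 1.0 and 80% power.

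- Two-sided 5%: n = 2(1.960 + 0.842)² × 1.0² / 0.5² = 62.8, so 63 per group. This matches.
- One-sided 5%, as the text states: n = 2(1.645 + 0.842)² / 0.25 = 49.5, so 50 per group. This does not match 63. It is a separate matter and nothing here depends on it.
- Dropout: 63 / 0.85 = 74.1, so 75 per arm and 150 in total. This matches.

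**How often chance would trigger adjustment.** With K independent covariates, each screened at p < 0.05, the chance of at least one apparent imbalance is 1 − 0.95^K:

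- K = 2: 9.8%
- K = 5: 22.6%
- K = 8: 33.7%

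The threshold and K are assumptions, because the article gives neither.

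**Precision at stake, by formula.** Assume baseline A1c correlates 0.5 with 12-month A1c and is always in the model. The residual variance is then 1 − 0.25 = 0.75. With 63 per arm, a difference of 0.5 and two-sided 5%, power ≈ Φ(0.5 / √(2v/63) − 1.96), where v is the residual variance.

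| Covariates beyond baseline | v | Approximate power |
|---|---|---|
| None | 0.75 | Φ(3.24 − 1.96) = 90.0% |
| Two at correlation 0.10, always included | 0.75 − 2(0.01) = 0.73 | Φ(3.28 − 1.96) = 90.7% |
| Three at correlation 0.20, always included | 0.75 − 3(0.04) = 0.63 | Φ(3.54 − 1.96) = 94.2% |

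Never adjusting rather than always adjusting therefore costs about 0.7 to 4.2 points. An imbalance screen adjusts some of the time, so its loss should fall within that.

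**Simulation on the same assumptions** (126 participants, two-sided 5%, screen at p < 0.10, 4,000 runs per setting, baseline A1c always included):

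| Further covariates | Type I error: screened | Always adjusted | Most favourable subset | Power: screened | Always adjusted |
|---|---|---|---|---|---|
| Two at 0.10 | 4.9% | 4.7% | 6.0% | 88.9% | 89.2% |
| Three at 0.20 | 4.3% | 4.9% | 8.3% | 90.7% | 93.8% |

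The power gaps are 89.2 − 88.9 = 0.3 and 93.8 − 90.7 = 3.1 points, in line with the formula. Allowing for simulation error and for other combinations of two or three covariates at 0.10 to 0.20, the ranges are about 0 to 4 points of power and roughly 6 to 10% type I error for the most favourable subset.

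**Why the mechanical rule is conservative.** Some false positives in the model without further covariates come from chance imbalance in a prognostic variable. The screen removes many of these, but keeps the larger standard error in the remaining trials.

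**The case against.** The strongest defence is the order of the text. A model with baseline values and a 12-month contrast comes first, and the sentence on adjustment opens by placing it afterwards. The natural reading is a primary test followed by a supplementary adjusted analysis. This stands. A reader might infer that the covariates of the primary model itself are picked after the data are seen, but the article does not say so. What remains is that it never states which estimate decides, while it also recommends the model partly for its capacity to take confounders.

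A reader might also infer that an unblinded team will choose covariates after seeing outcomes. The trial is described as a "prospective, multicenter, unblinded, parallel RCT", but that describes the trial. Nothing says who selects covariates or when, and the trigger concerns baseline variables, which are known without outcomes. Selective adjustment is left open, not planned.

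Nor does the stated rule inflate false positives, since a mechanical screen is conservative. Larger figures come from settings the article does not describe. Type I error of 11.8% arises from taking the best p-value over all subsets of three covariates at correlation 0.35. A power gap of 82% against 93% arises at the same correlation with baseline A1c left out, although the plan incorporates baseline values.

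Finally, a covariate list and a site term are commonly left to an analysis plan that is not shown, and their absence is no finding. That is right, but it does not dispose of the point. The article states a selection criterion, and an analysis plan that follows it inherits the fault.

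**Conclusion.** The concern holds in limited form. The plan fixes a poor criterion for adjustment beyond baseline values and leaves the decisive 12-month estimate unidentified. The initial contrast is not invalidated, and the sample size is unaffected.

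The size is modest: slight conservatism and about 0 to 4 points of power if the rule is mechanical, and a possible rise in type I error to roughly 6 to 10% if the most favourable subset were reported. These figures assume 63 evaluable participants per arm, two or three independent normal covariates at correlations of 0.10 to 0.20, a correlation of 0.5 for baseline A1c and a screen at p < 0.10. The article supplies only the arm size. Stronger or more numerous covariates would enlarge both effects. If age and sex alone were in play and weakly prognostic, both would sit at the low end.

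**What to change.** - Delete the criterion that ties adjustment to baseline differences between arms.
- Specify the 12-month mixed-model contrast with baseline A1c, the stratification factor site and, if wanted, age and sex, all included whatever the observed balance.
- Declare that estimate the single primary result, and label every other adjustment as sensitivity analysis.

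Diabetes duration would be an obvious further candidate, but the article mentions it only as an exclusion criterion. Whether it is recorded as an analysable variable would have to be confirmed first.

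The cost is a sentence or two in the analysis plan and a few degrees of freedom for the site terms. No extra data or participants are needed. The Results section reports recruitment as still open, so the change can be made before any outcome comparison.

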### Intervention

The participants randomly assigned to the intervention group will receive an iPhone 5S loaded with the *bant2* app, as well as a Bluetooth-enabled (a standard protocol for short distance wireless communication) Wahoo weight scale (Wahoo Fitness, Atlanta, GA, USA), a Jawbone UP24 (Jawbone, San Francisco, CA, USA) wrist-worn activity monitor, and a Jazz blood glucose meter (Agamatrix, Salem, NH, USA) [9]. We will also provide BlugluLe, a Bluetooth adapter that connects to the glucose meter and enables the wireless transfer of readings from the meter to the iPhone. The *bant2* mobile app also enables users to capture meal photos using the built-in camera, and track medication adherence on a weekly basis. In addition to the wrist-worn activity monitor, steps could also be tracked through the mobile phone itself using the built in accelerometer.

The *bant2* app, shown in Figure 1, facilitates self-monitoring of lifestyle behaviors, and enables patients to correlate their lifestyle behaviors with their glycemic control through paired (pre- and post-prandial) blood glucose testing [10]. Upon data capture, the app will assess the other data points in context, identify positive and negative behaviours based on the analysis, and faciliate remedial decision making. The app also enables patients to set goals and receive reminders, participate in a closed-gated social community, and accumulate points for positive behaviors, which can be redeemed for tangible gift cards (eg, groceries, gym memberships) [9]. This app builds on a previous version of the *bant* app, which focused on engaging adolescents in the self-management of type 1 diabetes mellitus (T1DM). A 12-week pilot of *bant* app demonstrated positive behavior change amongst the adolescents with T1DM [11].

We have ensured that all of the appropriate safeguards are in place to protect personal health information. For example, the iPhone requires a passcode to access the app, and the app itself requires a username and password. In the event that the device is lost or stolen, we can remotely wipe the device using mobile data management software (Airwatch, Atlanta, GA). The *bant2* app is intended to provide guidance and facilitate diabetes self-management, and is not classified as a medical device. Given that the app poses minimal risk to the patient, Health Insurance Portability and Accountability Act requirements do not apply.

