### Conclusions

This RCT is one of the first studies to evaluate an evidence-based mobile app that focuses on facilitating lifestyle behavior change driven by contextualized and structured SMBG. The results of this trial will provide insights regarding the usage of mobile tools for diabetes self-care, the effectiveness of consumer-grade devices for chronic disease management, the economic model of using incentives to motivate behavior change, and the consumption of test strips when SMBG follows a rigorously structured approach. The findings from this study will inform the next generation of diabetes education, guidelines for SMBG, and potentially inform health policy pertaining to strip reimbursements for T2DM patients that are not treated with insulin.

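### The component regression in Data Analyses cannot give independent effects of scale, activity monitor, SMBG and app features: only the whole package is randomised, so it gives associations with use

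*Protocol article*

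**What the plan says.** Trial Design describes a two-arm trial: "150 participants are randomly assigned to one of two groups", "with a 1:1 allocation ratio", where "the intervention group receives the mobile phone app system in addition to standard of care". The Intervention section lists what that arm gets. It starts with the phone and app ("The participants randomly assigned to the intervention group will receive an iPhone 5S loaded with the" app), continues with the scale ("as well as a Bluetooth-enabled (a standard protocol for short distance wireless communication) Wahoo weight scale"), and adds a wrist-worn activity monitor, a glucose meter and an adapter linking the meter to the phone. The app also awards points that can be exchanged for gift cards. Nothing in the article says that any part is randomised separately, withheld from some patients or introduced in stages.

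Data Analyses then plans a regression to apportion the result among activity monitor, weight scale, SMBG and app features. Its stated aim is to "determine their independent effects on the primary outcome at 12 months", and its stated yield is: "This approach will identify which aspect of the mHealth intervention contributed to the change in A1c". The Conclusions section expects the trial to give insight into, among other things, "the effectiveness of consumer-grade devices for chronic disease management, the economic model of using incentives to motivate behavior change".

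**The concern.** The wording promises causal attribution to single components, but the design compares one bundle with no bundle. Patients who use the scale or the meter often may differ from those who do not in motivation and general self-care, and patients may use a device more, or less, because of how their A1c is moving. A regression on use mixes these influences with any effect of the device. A component that does nothing could be credited with lowering A1c, and one that works could be missed. At stake is a secondary claim, on the primary endpoint, about which device or feature is worth providing.

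**Working it through.** The plan gives no figure for this analysis, so there is none to reproduce. The check asks what the design can identify, and then illustrates the consequence.

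**1. What randomisation identifies.** Inputs from Trial Design and Sample Size: two arms of 75. Input from Data Analyses: four named components. If each component is coded as provided or not, each of the four columns equals the arm indicator. An intercept plus four such columns is a 150 × 5 matrix of rank 2: one dimension for the intercept and one for arm. Only the package effect can be estimated from what was assigned.

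**2. What variation is left.** The article does not name the regressors. Within the intervention arm provision is constant, so component-level variation can come only from use. Across arms, controls may also self-test, since the Background says SMBG continues to be prescribed and controls receive usual care. That variation is not randomised either.

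**3. Whether the stated adjustments cover this.** The adjustment named in Data Analyses is for baseline characteristics that differ between groups, with age and sex as examples. Balance between arms does not address who uses what within one arm. The label of exploratory interest in the same section is attached to the contrasts at other time points. The component regression comes after it and carries no such label.

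**4. Routes of bias the article makes plausible.** The Discussion expects engaged patients to bring app data to consultations, with possible earlier medication changes. That is a route from engagement to A1c that is not specific to any one component. The Intervention section says steps may be recorded by the wrist monitor or by the phone, so measures of use overlap.

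**5. Illustration (assumed correlations, not document figures).** Take 63 evaluable intervention patients, the per-group number in Sample Size. Let four use measures have no true effect. One unmeasured motivation factor has correlation r with each use measure and −b with 12-month A1c, all in SD units. Any two use measures then correlate r², and each coefficient in the joint regression has expectation

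−r·b / (1 + 3r²).

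- r = 0.3, b = 0.2: −0.06 / 1.27 = −0.047
- r = 0.5, b = 0.5: −0.25 / 1.75 = −0.143

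The true value is 0 in both cases. In 1,500 simulated trials per setting, the percentage with at least one of the four components at p<0.05 was:

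| r | b = 0.2 | b = 0.3 | b = 0.5 |
|---|---|---|---|
| 0 (no confounding) | 18.0 | 17.5 | 19.1 |
| 0.3 | 18.9 | 29.0 | 48.1 |
| 0.5 | 25.3 | 34.0 | 62.7 |
| 0.7 | 20.7 | 30.2 | 55.3 |

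The first row reflects four unadjusted tests alone. At weak confounding nearly all the false-positive risk is of that kind. At stronger confounding most of it comes from motivation.

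**The case against.** The strongest reply is that this regression touches nothing essential. The primary analysis is the 12-month contrast between arms, and the component regression enters neither that test nor the sample size. That stands, and it sets the severity.

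A second reply is that the collinearity check rules out a model nobody proposed, because the article does not say that provision indicators are the regressors. That also stands in part. Step 1 shows what randomisation can deliver; it does not show that the planned model cannot be fitted. A regression on use can be fitted, and the objection to it is confounding. Choice of covariates may properly be left to the full protocol or SAP, but no choice of covariates turns a two-arm package design into randomised component contrasts.

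Third, independent effects is common shorthand for mutually adjusted coefficients. This softens the first phrase but not the second, which says the analysis will identify what contributed.

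Stronger readings that a reader might infer are not supported:

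- *That controls have none of the components.* This is too broad for SMBG, which may be part of their usual care.
- *That the incentive and strip-reimbursement statements rest on this regression.* Incentives are not named among its components, although they are built into the app. The article ties the strip question to consumption, and says only that findings may potentially inform policy.
- *That the article documents motivation or A1c progress as drivers of use in these patients.* Its remark on motivation (Participants) concerns people diagnosed within the past year, who are excluded, and it says nothing about A1c progress driving use. Both are plausible assumptions.

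**Conclusion.** The point holds as a should-fix on a secondary analysis. The design identifies one effect, that of the package against standard care, and none of the four component effects. The regression as planned gives associations between use and A1c, so the causal wording in Data Analyses is wrong as written. This follows from the two-arm design and the bundled provision. It assumes only that component variation means variation in use, since the article describes no other source.

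The size of any false attribution cannot be derived from the document. The simulated range of 19% to 63%, against about 18% to 19% without confounding, depends on the assumed correlations, and its low end is no worse than multiple testing alone. It shows what could happen and does not predict this trial. It would be a mistake to read the point as undermining the trial: the primary comparison is untouched.

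**What to change.** In Data Analyses, replace the two sentences on the component regression with:

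*Within the intervention arm, associations between use of each component and 12-month A1c, adjusted for baseline A1c, will be described as exploratory and non-causal.*

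This removes both "determine their independent effects on the primary outcome at 12 months" and "This approach will identify which aspect of the mHealth intervention contributed to the change in A1c". In Conclusions, limit statements of effectiveness, including the one on consumer-grade devices, to the whole package against standard care.

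Measuring use in a window before the outcome is optional. It lessens reverse causation but does not remove confounding by motivation. Separating component effects would need a design that randomises components, which is not proposed here.

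The cost is a change of wording and a weaker secondary claim. No additional patients or data are needed, and the primary analysis does not change.
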